#### **9.1.4.3.5 Modified Ashworth Scale (Appendix F) – Screening and Secondary Outcome Measure**

The Ashworth Score is a measure for assessing muscle tone and is commonly used in the assessment of patients with neurological disorders, particularly when assessing patients with spastic paralysis (Lee et al. 1989). The Modified Ashworth Score (MAS) is a modification of the Ashworth score. It is also a method used to assess muscle tone or muscle spasticity, and is primarily used in patients with central neurological disorders, especially stroke patients (Harb & Kishner 2022). It is more detailed and systematic in its assessment of muscle spasticity than the traditional Ashworth score and still uses a scale of 0 to 4, where 0 indicates no spasticity and 4 indicates severe spasticity, with each scale being clearly described (Blackburn et al. 2002).

The reliability and validity of the Modified Ashworth English version was relatively high with ICC=0.874-0.973 (Akpınar et al. 2017). The Chinese version had ICC=0.58-0.89 and highly correlated with BI (Barthel Index) ( $r=0.816$  to  $1.000$ ,  $p<0.01$ ) & with the motor component of Functional Independence Measure (M-FIM) total score ( $r= 0.935$  to  $0.981$ ,  $p<0.01$ ), indicating good reliability and validity (Li et al. 2014).

#### **9.1.4.3.6 36-Item Short Form Health Survey (Appendix G) – Secondary Outcome**

## **Measure**

The 36-Item Short Form Health Survey (SF-36) is a 36-item questionnaire designed to provide insight into a patient's health status and quality of life. Not only does this questionnaire cover a number of areas in a concise format, but the items are designed to provide a comprehensive assessment of the physical, psychological, and social dimensions of the patients (Patel et al. 2007). It includes aspects of physical functioning, limitations of physical role, social functioning, pain, and mental health (Laucis et al. 2015), etc.

The English version of SF-36 has ICC=0.96, associated with the Mental Component Summary MCS ( $r=0.72$ ,  $p<0.01$ ), showing relatively good reliability and validity (Russo et al. 1998). The Chinese version of the SF-36 was translated by Li et al. (2003). The Chinese version has Cronbach's  $\alpha=0.791$ , and structural validity,  $r>0.5$ , showing good reliability and validity (Zhang et al. 2012).

### **9.1.4.3.7 Brunnstrom Recovery Stage (BRS) (Appendix H) – Screening Outcome Measure**

The Brunnstrom Recovery Stage (BRS) is a brief and easy-to-administer measure used to assess motor function. BRS consists of three items for the arm (BRS-A), hand (BRS-H), and leg (BRS-L), all of which are scored on a 6-point Likert-type scale, with each stage representing a different motor characteristic and change in muscle control (Shah et al. 1986). These items are usually used individually to describe the patient's motor function (i.e., arm, hand, and leg, respectively).

The reliability and validity of the English version of the BRS were relatively good, in which it was highly correlated to the Modified Modified Ashworth Scale (MMAS) scores ( $r = 0.81$ ,  $p < 0.0001$ ) (Naghdi et al. 2010). The Rasch reliabilities of the upper-extremity items and overall motor items were high (0.91–0.92) (Huang et al. 2016).

### **9.1.4.3.8 Saint Louis University Mental Status (SLUMS) Examination (Appendix I) – Screening Outcome Measure**

The Saint Louis University Mental Status (SLUMS) Examination is a measure used to

assess cognitive functioning, specifically for early detection and monitoring of mild cognitive impairment and early stages of dementia (Tariq et al. 2006). SLUMS includes assessments of several cognitive domains such as attention, memory, executive functioning, orientation, and numeracy (Cao et al. 2012). Specific items include vocabulary learning, memory recall, numeracy, clock drawing, number reversal, and image naming (Shwartz et al. 2019). It is scored on a 30-point scale, with higher scores indicating better cognitive functioning and lower scores suggesting impaired cognitive functioning. Items are designed to cover multiple cognitive domains to provide a more comprehensive assessment.

The English version of SLUMS has ICC=0.990-0.998 and correlated with Montreal Cognitive Assessment (MoCA) score ( $r=0.831, p<0.0001$ ), showing good reliability and validity (Noyes et al. 2023). (Naghdi et al. 2010). The Chinese version of the SLUMS was translated by Zhang et al. (2021). The Chinese version had Cronbach's  $\alpha=0.723$ , ICC=0.990-0.998 ( $p<0.05$ ), at a score of 23.5, the sensitivity & specificity were 0.738 & 0.725, respectively, showing that the reliability and validity were relatively good (Zhang et al. 2021).

Permission to use the simplified Chinese version has been obtained from the author of this translated version, Third Hospital of Soochow University (Appendix J2).

#### **9.1.4.4 Pressure Garment Application Form (Appendix J)**

The Pressure Garment Application Form is a self-developed form that includes items pertaining to pressure garment application including wearing time of pressure garment, frequency and length of occupational therapy session, and caregiver participation, etc. This form will be filled out by the participants or their family member on a daily basis and will be supervised by their therapists.

#### **9.1.5 Data Collection**

Participants will be asked to read the Phase I information sheet (Appendix A) and sign the written informed consent form (Appendix L) before participating in this phase of

study.

This study will involve Therapists A and B (n: Therapist A=3; Therapist B=6) from all three participating hospitals. Therapists selected will need to have a bachelor's degree or above, and with minimum of three years of relevant work experience. The therapists will be labelled as: Therapist A, who will serve as an assessor and blinded; Therapist B, who will serve as the participant's treating therapist and blinded. The study will also include a pressure garment fabricator. The fabricator (a therapist, a researcher, or a professional tailor) must have experience in pressure garment fabrication.

Prior to the data collection, all the therapists will receive an 8-hour training on pressure garment from the pressure garment fabrication expert, whom is one of the supervisory team members. The tentative training programme is shown below:

| Time          | Content                                                                             |
|---------------|-------------------------------------------------------------------------------------|
| 08:30 – 09:00 | Registration and welcome; Introduction to the purpose of the training and programme |
| 09:00 – 10:00 | Basics of pressure garment                                                          |
| 10:00 – 10:15 | Coffee break                                                                        |
| 10:15 – 12:15 | Pressure garment measurement and pattern making I                                   |
| 12:15 – 12:45 | Education on care of pressure garment care                                          |
| 12:45 – 13:45 | Lunch break                                                                         |
| 13:45 – 14:30 | Pressure garment measurement and pattern making II                                  |
| 14:30 – 15:00 | Putting on and adjusting pressure garment                                           |
| 15:00 – 15:15 | Coffee break                                                                        |
| 15:15 – 16:30 | Simulated practical session and group exercise                                      |
| 16:30 – 17:00 | Programme summary                                                                   |
| 17:00 – 17:30 | Q&A                                                                                 |

For randomization purposes, the researcher will generate 165 sequences that contains equal numbers of 1 (S-10), 2 (DD-10), and 3 (S-0) using a computerized software SPSS 26.0. The sequence will be store electronically. The process of data

collection will then proceed with participant recruitment. This recruitment will be done by placing posters that contain the relevant information of this study, including the study objectives, procedures, and duration alongside contact information, etc. in the three hospitals as permitted. Interested patients can contact the researcher of this study. Recruitment will also be done through recommendation made by therapists who are involved in treating stroke patients. Before enrolling into the study, potential participants will be screened using MAS, SLUMS, and BRS by Therapist A. Only those who meet the inclusion will be enrolled. Prior to the enrolment, the potential participants will need to read the information sheet (Appendix L) and sign the written informed consent form (Appendix M). Participants will be asked to complete the Demographic Form (Participant) (Appendix A).

After participant enrolment, Therapist A will report to the researcher to obtain the randomization sequence number generated using SPSS 26.0. The researcher will assign the participant into either S-10 (intervention group), DD-10 (intervention group), or S-0 (placebo group) according to the sequence list. Therapist A, a blinded therapist will then proceed with taking the baseline data or Time 1 (start of trial), including FMA, BBT, MAS, VAS, DASH, and SF-36. After that, Therapist A will take the pressure garment measurement and then, give the pressure garment measurement to the pressure garment fabricator for pressure garment custom fabrication. Upon receiving the two pairs of pressure garment (within 7 days after pressure garment measurement), the participant will try it on for 30 minutes, under the supervision of Therapist B, a blinded therapist. The participant will formally be enrolled in the study if he/she does not experience allergy, oedema, pain or any other discomfort. All participants will be asked to wear the provided pressure garment for 3 hours in the morning, 3 hours in the afternoon, and 8 hours at night each day for 8 weeks.

During Phase IA, i.e., the first four weeks between Time 1 (Baseline) and Time 2 (Week 4), when participants are hospitalized in the rehabilitation department of the hospital, he/she will be required to attend an occupational therapy session conducted by Therapist B once a day for 30 minutes, 5 days a week. During Phase IB, i.e., the second

four weeks between Time 2 (Week 4), and Time 3 (Week 8), when participants were being discharged from the hospital. Although they need to continually wearing the pressure garment according to same wearing schedule, they will not need to attend occupation therapy session.

Each participant will be given a Pressure Garment Application Form (Appendix K) to complete. The form will need to be returned to the researcher during Time 2 (Week 4) assessment. A new form will be given for the participant to complete and collected by the researcher during Time 3 (Week 8) assessment. Therapist B will constantly monitor the condition of the pressure garment to make sure it stays tightly fit throughout the study. Depends on the garment condition, torn or loosed pressure garment will be repaired or replaced using a new pair of garments.

For Time 2 (Week 4) and Time 3 (Week 8) assessments, the FMA, MAS, BBT, and VAS will be performed by Therapist A. The DASH and SF-36 will be administered by Therapist A and completed by the participant; however, if needed, it can be completed with the help of a caregiver or a therapist. The MAS will be assessed immediately after removal of the pressure garment, and the DASH, and SF-36 will be completed within 30 minutes of removal. The order of assessments will be determined by drawing a ballot. The FMA, BBT, VAS will be assessed 30 minutes after removal and the order of assessment will also be determined by drawing a ballot.

Phase IA = Pressure Garment + Occupational Therapy for 4 weeks

Phase IB = Pressure Garment for 4 weeks

Therapist B, a treating therapist will provide a list of specific occupational therapy interventions, identified in this study as representing routine practice to participants. Therapist B will record the Pressure Garment Application Form (Appendix K). These specific occupational therapy interventions will be given according to the following sequence:

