## **9.0 Research Methodology**

### **9.1 Multicentre, Double-Blind, Prospective Randomised Controlled Trial** (Research Question 1; Specific Objective 1; Hypotheses 1 to 7)

#### **9.1.1 Research Design**

Multicentre, double-blind, prospective randomised controlled trial will be used as it involves three research locations, blinding of participants and therapists, and prospective randomization of the participants into different intervention groups or placebo group.

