##### **9.1.2.1 Inclusion and Exclusion Criteria**

Inclusion criteria:

1. Between 18 and 80 years of age
2. Within 1 – 12 months of ischemic or haemorrhagic stroke
3. First onset resulting in hemiparesis of a limb with Brunnstrom Recovery Stage (BRS)

of 3, 4 or 5 (Naghdi et al. 2010)

4. Modified Ashworth Scale (MAS) with scores of less than or equal to level 2 for elbow, wrist, and hand muscle tone in the affected upper extremity (Harb & Kishner 2022)

5. Able to understand instruction

Exclusion criteria:

1. Serious cardiovascular or respiratory diseases
2. Skin lesions, infections or other skin problems
3. Serious circulatory problems such as deep vein thrombosis
4. Allergies or significant discomfort to pressure garment materials
5. Upper extremity fractures or severe joint problems
6. Severe cognitive impairment with Saint Louis University Mental Status (SLUMs) scores equal to or less than 27 (above high school level of education)/25 (below high school level of education).

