#### **9.1.2.3 Sample Size Calculation**

Sample size was calculated using G\*Power 3.1. Assuming that the data is normally distributed, this study will use mixed model ANOVA to compare differences between

the effects of DD-10, S-10, and S-0 pressure garment on sensorimotor functions and quality of life among stroke patients at three different time points during the 8 weeks of application. With small to medium effect size,  $f$  of 0.125, power of 0.8,  $\alpha$  error of 0.05, three groups, and three measurements, the total sample size needed will be 132, as shown in Figure 4. With 44 people in each group and taking into account the 20 % dropout rate, by using the formula:  $N = n/(1-d)$ , i.e.,  $44/(1-0.2) = 55$ , there will be a total of 55 people in each group. Thus, the final sample size will be 165 patients ( $n$ : DD-10 Group = 55; S-10 Group = 55; S-0 Group = 55).

[figure not shown]

Figure 4. Sample Size Calculation

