### **9.1.6 Data Analysis**

Data will be analysed using SPSS 26.0 using Intention-to-treat (ITT) analysis. ITT analysis, which aims to minimize bias and maintain random allocation of study participants (Gupta 2011), is suitable to be used when there are shedding participants. Its key idea is to analyse the group to which the participant belongs in that initial allocation, regardless of whether they completed the study or received the intended intervention. In clinical trials, participants may drop out, refuse intervention, or deviate from the study protocol. The ITT analysis includes all participants regardless of whether they completed the study or followed the treatment plan. This helps prevent shedding bias, which may occur if only completers are analysed (Mccoy 2017). The study will use a imputation method, such as, Last Observation Carried Forward (LOCF) (Shao & Zhong 2003) or mean imputation (Jadhav et al. 2019), or multiple imputation (Austin et al. 2021), this will probably depend on the requirements of the data.

Both descriptive and inferential statistics will be used. Frequencies, means, and medians will be used to describe the demographic data (Fisher & Marshall 2009). A mixed model ANOVA to compare the outcome measures.

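### One unstratified list of 165 serves three hospitals, so arms are balanced overall but only by chance within each hospital; hospital-specific lists would be a cheap improvement

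*Protocol*

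**What the plan says.** Section 9.1.1 calls the trial multicentre because "it involves three research locations". Section 9.1.5 describes the allocation list: "the researcher will generate 165 sequences that contains equal numbers of 1 (S-10), 2 (DD-10), and 3 (S-0"). Each enrolled participant is then given DD-10, S-10 "or S-0 (placebo group) according to the sequence list". The totals match section 9.1.2.3 ("DD-10 Group = 55; S-10 Group = 55; S-0 Group = 55"). No block, stratum or separate hospital list appears anywhere in the protocol.

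On staff, section 9.1.5 states: "This study will involve Therapists A and B (n: Therapist A=3; Therapist B=6) from all three participating hospitals". Therapist A performs the FMA (the primary outcome), BBT, MAS and VAS. One assessor and two treating therapists per hospital is the natural reading, though it is not stated outright.

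Section 9.1.3 asserts that the hospitals are equal in facilities and expertise, but reports 50, 35 and 36 beds and 20, 14 and 15 rehabilitation therapists. Eligibility is "Within 1 – 12 months of ischemic or haemorrhagic stroke". The one sentence on the inferential model, in section 9.1.6, reads "A mixed model ANOVA to compare the outcome measures" and names no further terms.

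**The concern.** Equal totals across 165 codes say nothing about the split inside a hospital. If each hospital has its own assessor and treating therapists, hospital brings together rater, local case mix and whatever treatment is given beyond the standardised 30-minute occupational therapy session. Appendix A records physiotherapy, traditional Chinese medicine and other treatments, so the protocol itself expects these to vary. Recovery rate may also vary, since patients enter from 1 to 12 months after stroke.

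At stake are the precision of the primary comparison and how easily its result can be defended if one arm turns out to be concentrated in one hospital. List construction has to be settled in the protocol before the first patient is allocated. An analysis plan written later cannot change it.

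**Working it through.** **1. The protocol's own figure.** Inputs from section 9.1.2.3: f = 0.125, alpha 0.05, power 0.80, three groups, three measurements. Assumed, because the text does not state them: correlation 0.5 between measurements, and sphericity. For the group-by-time interaction, λ = f²·N·m/(1−ρ) = 0.015625 × 132 × 3/0.5 = 12.375, with df 4 and (132−3)×2 = 258. Power is 0.808, so N = 132 is reproduced. The within-factor version gives 105 and the between-factor version 417. Dropout: 44/(1−0.2) = 55 per arm, 165 in total. The planned test is therefore best read as the group-by-time interaction.

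**2. Imbalance within hospital.** The protocol gives no recruitment target per hospital, so the splits are assumed. For a hospital of 55 drawn from a 55/55/55 list, the difference between two arms has variance 55 × (110/164) × (2/3) = 24.6, an SD of 5.0. From 20,000 random permutations of the list:

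| Assumed hospital sizes | Mean of largest gap | Gap of 8 or more in some hospital |
|---|---|---|
| 55/55/55 | 8.0 | 54% |
| 70/55/40 | 7.9 | 52% |
| 100/40/25 | 7.3 | 44% |

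The gap is the largest minus the smallest arm, taken at the worst of the three hospitals. For one given hospital of 55 the mean gap is 5.9, and it is 8 or more in 28% of lists.

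**3. What the imbalance does to the test.**
- *Stable offset.* If hospital h adds a constant to every score, change from baseline is (Y + h) − (Y₀ + h) = Y − Y₀. The offset is gone, and the interaction F is unchanged. Offsets of −5, 0 and +5 added by hospital to simulated data left F exactly as it was.
- *Type I error.* In simulated one-way comparisons with one unstratified list and no hospital term, it was 0.044 to 0.053 with hospital explaining 2% to 20% of variance.
- *Size of the chance shift.* For a single score with 55 per arm, the standard error of an arm difference is √(2/55) = 0.19 SD. The part due to hospital has SD of about 0.19 × √v, which is 0.04 at v = 0.05 and 0.07 at v = 0.15.

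**4. Precision, if hospitals differ in change.** Let v be the share of the variance in change explained by hospital (assumed 5% to 15%). Take a comparison of change in 132 patients with power 0.78 when hospital is left out (λ = 9.41, df 2 and 129). A hospital term raises λ to at most 9.41/0.95 = 9.91 or 9.41/0.85 = 11.07, which gives ideal power of 0.80 and 0.85. About 0.80 to 0.83 is the more cautious range. In a separate simulation with 165 patients and an assumed effect of 0.6 SD in one arm, the term raised power from 0.908 to 0.933 at v = 0.10.

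**5. Stratifying without the term.** With arms balanced inside hospitals, the arm mean square loses the hospital variance while the residual keeps it. For one change score in 165 patients, type I error is about P(F > 3.05/(1−v)) on 2 and 162 df. At v = 0.15 this is P(F > 3.59) = 0.03. Simulation gave 0.035 at v = 0.10 and 0.025 at v = 0.20. The test becomes conservative.

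**The case against.** The best defence is that unstratified randomisation is valid. The comparison is unbiased in expectation, type I error holds, and the trial does something to make the hospitals alike: a fixed occupational therapy sequence and common therapist training (on garments, not on FMA scoring). All of that stands, and it makes this an improvement rather than the repair of an error.

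Four stronger readings are tempting, and the document does not support them.
- A reader might infer that the primary comparison is biased. It is not: the imbalance is chance, and the likely shift is small beside the standard error.
- A reader might infer that differences between assessors in FMA scoring distort the result. A stable difference cancels in the group-by-time test. Only rater drift or hospital differences in change would matter.
- A reader might infer that the analysis ignores hospital and time since stroke. Section 9.1.6 is merely silent, and an analysis plan that is not shown may supply these terms.
- A reader might convert v into patients: 1/(1−v) − 1 gives 5% to 18% for v = 0.05 to 0.15. That holds only if v is a share of the variance in change, and the protocol gives no figure for it.

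The objection does not reach the list itself, which the protocol fixes.

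**Conclusion.** The point holds as a modest design weakness. One list for three hospitals leaves within-hospital balance to chance, and a largest gap of about 8 patients is typical under the assumed splits. Validity is not threatened. The loss is one of precision and credibility, and it arises only if hospitals differ in recovery rate, case mix or other treatment. Its size, roughly two to five points of power, rests on an assumed 5% to 15% of the variance in change. The imbalance figures rest on assumed hospital sizes but move little across them. One assessor per hospital is an inference from "n: Therapist A=3; Therapist B=6) from all three participating hospitals".

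**What to change.** Before the first allocation, replace the single list with three hospital-specific lists in randomly varied permuted blocks, for example of 6 and 9. Keep the lists and block sizes from Therapists A and B. A block of 9 holds three codes per arm, so the gap in any hospital cannot exceed 3. Blocks of 3 are better avoided: the third code is certain once two are known, and the DD-10 garment is built differently from the single-layered ones.

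Because allocation is then stratified, state that the mixed model includes hospital and hospital-by-time. A hospital main effect alone does not alter the group-by-time test, and leaving both out makes it conservative. Do not add baseline FMA as a covariate while baseline is also Time 1 of the outcome.

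The sample size is unchanged, and no visits are added. Two costs remain: allocation within a site becomes slightly more predictable, and exact totals of 55 per arm are no longer guaranteed, since each hospital may end in mid-block (at most 3 per hospital, so 9 overall in the worst case).

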#### **9.1.2.2 Sampling Method**

Participants will be recruited through convenience sampling. Convenience sampling is a common sampling method whose core features are convenience and economy (Sedgwick 2013). When conducting convenience sampling, the researcher selects those samples that are easily accessible, rather than obtaining samples through random selection. This means that the sample is usually chosen based on the convenience of the researcher, such as choosing volunteers or those who are easily accessible (Stratton 2021). It can help the researcher to obtain data quickly, but potential biases and limitations must be carefully considered when analysing and interpreting the results (Etikan et al. 2016).

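### Allocation is not concealed from the researcher, who generates and applies the list and is also the contact for patients answering the posters

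*Protocol*

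**What the plan says.** All the relevant steps are in Protocol 9.1.5 (Data Collection), in this order:

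1. The list is made first: "For randomization purposes, the researcher will generate 165 sequences that contains equal numbers of 1 (S-10), 2 (DD-10), and 3 (S-0". On its custody the protocol says only: "The sequence will be store electronically".
2. Recruitment starts after that. There are two routes. For the posters, "Interested patients can contact the researcher of this study". For the other, "Recruitment will also be done through recommendation made by therapists who are involved in treating stroke patients".
3. Therapist A, described as blinded, screens with MAS, SLUMS and BRS.
4. After enrolment, Therapist A asks the researcher for the sequence number, and "The researcher will assign the participant into either S-10 (intervention group), DD-10 (intervention group), or S-0 (placebo group) according to the sequence list".
5. Therapist A then takes the baseline outcome measures and the garment measurements, and the garment is made.
6. The participant tries on the assigned garment for 30 minutes and is formally enrolled only if there is no discomfort.

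Section 9.1.1 lists participants and therapists as blinded, and 9.1.5 lists Therapists A and B. Neither lists the researcher. No independent list holder, central service, sealed envelopes or access limit is mentioned.

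**The concern.** Randomisation protects the comparison only if nobody who can influence a patient's entry knows the next assignment. Here one role makes the list, reads each arm from it, and hears from prospective patients beforehand. Entry is open from 1 to 12 months after stroke (9.1.2.1), and a recruitment contact could easily learn where in that window a patient stands. If patients with better recovery prospects tended to go forward when a compression code was next, and others when S-0 was next, the arms would differ in Fugl-Meyer change without any garment effect.

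Blinding of participants and assessors acts after allocation. Intention-to-treat analysis preserves the groups as allocated, including any imbalance built in at entry. Covariate adjustment, if added, corrects only for what was recorded.

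The order of steps adds to this. Because formal enrolment follows the try-on of the assigned garment, final acceptance into the trial comes after the arm is fixed.

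**Working it through.** **The plan's own sample size, as a starting point.** Section 9.1.2.3 gives f = 0.125, power 0.80, alpha 0.05, three groups, three measurements, N = 132. For the group-by-time interaction, with correlation 0.5 and sphericity assumed (the text states neither):

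- λ = f²·N·m/(1 − ρ) = 0.015625 × 132 × 3 / 0.5 = 12.375
- df = (3 − 1)(3 − 1) = 4 and (132 − 3)(3 − 1) = 258
- power = 0.808, and N = 132 reproduces
- dropout: 44/(1 − 0.2) = 55 per arm, 165 in total

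Concealing the list changes none of this.

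**Who can see the next arm at each step (9.1.5).**

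| Step | Who | Could know the next arm? |
|---|---|---|
| Generate list | Researcher | Yes |
| Contact with poster responders | Researcher | Yes |
| Recommendation by treating therapists | Therapists | No access described |
| Screening | Therapist A (blinded) | No, as described |
| Assignment | Researcher | Yes |
| Baseline tests | Therapist A (blinded) | Arm already assigned |
| Try-on and formal enrolment | Therapist B (blinded) | Arm already assigned |

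The exposed step is the second row: who goes forward among poster responders, and when.

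**Size, as an illustration.** The documents give no figure for steering, so the following are assumptions:

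- No true effect; 44 analysed per arm; change score with SD 1; one-way F test at 0.05. This is simpler than the planned mixed ANOVA.
- In a share q of slots the researcher can choose between two waiting candidates. The better prospect goes to a compression arm and the worse to S-0, always in that direction.
- Perceived prognosis correlates ρ with the outcome.

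The expected better and worse of two standard normal values differ by 1.128, so the bias is d = q × 1.128 × ρ. With arm means d/2, d/2 and −d/2, the deviations from the grand mean are d/3, d/3 and −2d/3, and their squares sum to 2d²/3. Hence λ = 44 × 2d²/3, with 2 and 129 degrees of freedom.

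| q | ρ | Bias d (SD) | False-positive rate |
|---|---|---|---|
| 10% | 0.3 | 0.03 | about 5% |
| 10% | 0.5 | 0.06 | about 6% |
| 20% | 0.3 | 0.07 | about 6% |
| 20% | 0.5 | 0.11 | about 8% |
| 30% | 0.3 | 0.10 | about 7% |
| 30% | 0.5 | 0.17 | about 12% |
| 30% | 0.7 | 0.24 | about 19% |

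For example, q = 0.2 and ρ = 0.5 give 0.2 × 1.128 × 0.5 = 0.113. Simulation under the same model agrees with these values.

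A second steering model sets the prognosis gap of steered patients directly, at 0.5 to 1.0 SD. It gives 5.5% to 7.2% with 10% steered, 7.2% to 14.6% with 20%, and 10.2% to 28.1% with 30%.

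**The case against.** The strongest reply is that the protocol does separate some roles. Screening belongs to Therapist A, who is blinded, and the number is released only after enrolment. There are three such therapists, and some patients arrive by therapist recommendation, a route for which no researcher step is described. All of this stands and narrows the exposure considerably. It does not close it, because poster responders reach the researcher before they reach the screener.

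It is also fair that the text never says the researcher keeps the list or that the list is open. It says only that the list is stored electronically. But a role that generates the list and assigns from it has access unless something prevents that, and nothing is described.

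The size rests on invented inputs: the steered share, the correlation, two candidates waiting, and steering always in one direction. That objection stands in full. At 10% steering the effect on the error rate is slight.

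Two stronger readings are tempting and should not be made:

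- A reader might infer from 9.1.2.2 that the researcher hand-picks the sample, since it says "the researcher selects those samples that are easily accessible, rather than obtaining samples through random selection". That sentence is a general definition of convenience sampling and assigns no task in this trial.
- A reader might infer that the equal counts of 55 make the sequence predictable to anyone keeping a tally. Someone with only the running counts would guess right about 39% of the time, against 33% by chance, and the therapists and participants are described as blinded to past assignments. This adds almost nothing.

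**Conclusion.** The point holds in a limited form. As written, 9.1.5 lets the next arm be known to a role that can influence which poster responders go forward and when, and it describes no concealment from that role. Baseline testing and formal enrolment also come after assignment. The documents show that selection bias can enter. They do not show that it will, nor that the next arm is known to whoever screens.

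Under 20% to 30% steering and a correlation of 0.3 to 0.7, the bias would be about 0.07 to 0.24 SD and the false-positive rate about 6% to 19%. These figures are conditional illustrations, not estimates for this trial. They matter because the trial is powered for a small-to-medium effect and because such a bias cannot be reliably removed once patients are allocated. It should be corrected before recruitment starts.

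**What to change.** Rewrite the allocation paragraph in 9.1.5 as follows:

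- A supervisory-team member with no recruitment, treatment or assessment role generates and holds the list. The recruiting researcher has no access to it during recruitment.
- The order is: eligibility, consent, baseline tests and limb measurements, all recorded under the participant ID; then release of the next code, to the garment fabricator only.
- Every participant whose code has been released counts as randomised for the intention-to-treat analysis, whatever happens at the try-on.
- The recruiting researcher is not the fabricator. Section 9.1.5 allows the fabricator to be a therapist, a researcher or a tailor, so if the two coincide, the roles must be separated within the existing team.

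The cost is one paragraph and a transfer of the list, with no extra visits and no change to the 165. The researcher loses sight of the list during recruitment, and the order of steps shifts slightly because baseline moves ahead of assignment. If a concealed procedure is already intended, writing it down is enough.
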